## Abstract

**Background:**

Examining the role of sex on recovery from pediatric TBI (pTBI) is a complex task, specifically when referring to injuries occurring during critical developmental and maturation periods. The effect of sex hormones on neurological and neuropsychiatric outcomes has been studied among adult TBI females, but not in children. During development, puberty is considered a key milestone accompanied by changes in physical growth, neuronal maturation, sex hormones, and psychological symptoms. Following pTBI, such changes might have a significant effect on brain re-organization and on long-term neuropsychiatric outcomes. While hormonal dysfunction is a common consequence following pTBI, only few studies have systematically evaluated hormonal changes following pTBI.

**Aims:**

To describe a multimodal protocol aimed to examine the effect of puberty on brain connectivity and long-term neuropsychiatric outcomes following TBI in female girls and adolescents.

**Methods:**

A case-control longitudinal prospective design will be used. 120 female participants aged 9 to 16 years (N = 60 per group) will be recruited. In the acute phase (T0-1 month), participants will undergo an MRI protocol for brain connectivity, as well as a clinical evaluation for puberty stage and hormonal levels. In the chronic phase (T1-18-24 months), participants will complete a neuropsychiatric assessment in addition to the MRI and puberty evaluations. Hormonal levels will be monitored at T0 and T1. A moderation-mediation model will be used to examine the moderating effects of puberty on the association between pTBI and neuropsychiatric symptoms in female girls and adolescents, through the mediating effect of brain network connectivity.

**Significance:**

This study will highlight sex-specific factors related to outcomes among females following pTBI and enhance our understanding of the unique challenges they face. Such information has a substantial potential to guide future directions for research, policy and practice.

## Introduction

In the last decade, policy statements have been made by funding agencies regarding the requirements for the consideration of sex and gender [1] in research, emphasizing the fundamental contribution of these factors for good scientific practice [1, 2] (in our study we will refer to sex as the endogenous variable, although we acknowledge that sex and gender constructs are interconnected and not binary). The World Health Organization (WHO) Disability and Rehabilitation Action Plan 2014–2021, also calls for including age and sex data in policy documents among individuals with developmental and acquired disabilities [3], such as brain injury. Traumatic brain injury (TBI) is considered a silent epidemic, as the major post-TBI disabilities, predominantly neuropsychiatric, are not immediately apparent. Furthermore, sex effects on the pathophysiology and recovery are poorly understood. In recent years there is a growing recognition of a *male bias* problem, with predominantly rodent males used in preclinical TBI designs and fewer females than males recruited to clinical trials. Without research, which focuses specifically on the mechanisms and outcome of females with TBI there is a risk that clinical care, policy development and advocacy services will not effectively accommodate post-TBI females.

Outcomes following TBI show that females experienced worse outcomes beyond injury severity [4], took longer time to recover [5], showed higher post-concussive symptoms [6], greater cognitive decline [7], and a higher risk of depression compared to males [8, 9]. In contrast, a recent review found better quality of life [10] and better cognitive functioning [11] among females following TBI, as compared to males. Such inconsistencies in the literature require an in-depth evaluation of additional factors that may affect recovery and outcome post TBI focusing not only on sex-differences, but rather on sex-specific factors.

Sex hormones, (specifically gonadal hormones such as estrogen and progesterone) have been suggested as significant factors mediating neurological and neuropsychiatric outcomes after TBI in females [12, 13]. A possible explanation, known as the *hormonal withdrawal hypothesis* (i.,e, frequent miss of menstrual periods or total absence of menstruation), has been reported in females following TBI [13], and suggested to be a key factor contributing to worse outcomes in females. Furthermore, as males have low pre-injury levels of gonadal hormones, they may be less affected by hormonal suppression post injury. The phase of the menstrual cycle at injury, was found to be significantly related to psychological and neurologic outcomes among females following mild TBI [13]. Females with the highest progesterone levels at the time of injury (i.e., luteal phase of the menstrual cycle) had the worst outcomes as compared to females in the follicular phase (i.e., relatively low progesterone levels) and compared to females taking synthetic progestin (i.e., maintaining high levels of progestin before and after injury). Thus, if the hormonal withdrawal hypothesis is linked to poorest outcomes, a relatively simple intervention could lead to significant improvement in outcomes [13] necessitating the need to address hormonal levels and time of menstrual cycle across studies with female TBI patients of all ages.

While there is paucity of data on the effect of sex on neurological and psychological outcomes in adult TBI females, there is even sparser literature on such sex effects among female girls and adolescents. Pediatric-TBI (pTBI), a leading cause of disability in children and adolescents [14] can lead to physical, neurological, cognitive and neuropsychiatric disorders [15, 16]. Many factors have been shown to affect outcomes of pTBI, among them are: pre and post-injury environmental factors [17], injury severity [18], time since injury [19, 20], and child’s sex and age at injury [15, 21, 22]. During development, age may mask differences in outcomes related to the role of sex on recovery, specifically when referring to injuries occurring during critical developmental and maturation periods. Emerging literature suggests that both the response to injury and the path to recovery may differ between male and female children and adolescents [21, 23]. Unfortunately, research on pTBI seldom separates females and males in their analyses [24], and the literature on outcomes is relatively limited. A recent study revealed that pTBI patients had a 3.2-fold higher odds of being diagnosed with an endocrine disorder, with even higher rates in females compared to males [25]. Both early and late endocrine changes can occur after pTBI including acute alterations in the hypothalamic-pituitary-adrenal (HPA) axis, and disturbances in puberty [26, 27]. In addition, an interaction between sex, and neuropsychiatric symptoms following pTBI was reported, with males affected more than females [28], and females being at a higher risk for developing internalizing symptoms (e.g., depression and anxiety) [29], while males tend to present more externalizing problems (e.g., impulsive and aggressive behaviors) [30].

Hormonal dysfunction following pTBI is common and can evolve, resolve, or persist after injury [31]. It is not clear how much of the puberty related hormonal changes contribute to variation in pTBI outcomes [31]. Puberty is a key developmental milestone accompanied by substantial physical growth, neurologic changes, peak levels of sex hormones, and changes in emotional and behavioral symptoms [32]. It encompasses a combination of two distinct brain activated hormonal processes, adrenarche (the activation of the HPA axis) and gonadarche (the reactivation of the hypothalamic-pituitary-gonadal axis), which together lead to a dramatic rise in the circulating levels of sex hormones [33]. Puberty is associated not only with an increase in hormone levels, but also with dramatic fluctuations in the levels of estrogen circulating in the body [34]. Subsequently, the body’s systems must rapidly adapt to higher and fluctuating levels of hormones that may influence mood and other emotional symptoms. Recently, a large cohort study [35] demonstrated that earlier onset of puberty (pubescence) was associated with higher risk of depression and anxiety in females but was unrelated to the presence of depression in males. The gap between the onset of emotional changes and full maturation of inhibitory brain mechanisms may contribute to a window of risk for emotional dysregulation and other neuropsychiatric symptoms during puberty [36]. Paucity of studies have indicated that pubertal status predicts sex difference in the prevalence of neuropsychiatric symptoms better than age, suggesting that sex hormones play a significant role in the pathophysiology of neuropsychiatric disorders [34]. Furthermore, it should be acknowledged that age and pubertal maturation are highly correlated, arising the need for research designs that explicitly disentangle puberty and age effects on pTBI outcomes [37]. This requires the comparison between females with and without pTBI within the same age range and puberty phase.

Studies of pTBI survivors have reported high prevalence of pituitary dysfunction related to hormonal deficiency (hypopituitarism) at 1–5 years post injury [38]. Interestingly, injury severity did not predict endocrine outcomes. In a recent study, p-TBI patients had about 3-times the risk of a central endocrine diagnosis compared to the general population. Moreover, females had a shorter time gap between the injury and the endocrine disorder compared to males [25]. Probable pubertal adolescent females (13–18 years) had a reduced mortality rate compared to males. These findings suggest that post-injury elevation in hormonal levels among young females may propose an opposite profile to the withdrawal hypothesis reported in adult TBI females.

The relationship between puberty and brain development is likely to be complex and nonlinear, and interacting with the distinct but synchronous effects of age [33]. There is evidence for brain structural development associated with pubertal maturation [39, 40] with different trajectories seen in males and in females [39, 41]. Evidence of a strong relationship between white-matter fiber density and age, sex, and puberty during development has been reported [42, 43]. Physical pubertal changes predicted patterns of changes in structural connectivity, and pubertal processes contributed to distinct changes in males and females across brain development [44]. Studies using structural brain network graph theory revealed an early separation between developmental trajectories of males and females, with male adolescents displaying higher structural intra-hemispheric connectivity and females displaying higher inter-hemispheric connectivity [45]. Although studies on brain connectivity and pubertal hormones are limited, there is evolving evidence for the hypothesis that sex-hormones are related to the microstructure of white-matter and that pubertal development may be associated with maturation of structural connectivity above and beyond chronological age [46].

Taken together, the current research question forms a moderated-mediation model using a longitudinal case-control design. The main aim of the proposed study is to examine the moderating effect of puberty (pre-and post-pubescence) in females, on the association between brain network connectivity and neuropsychiatric outcomes in girls with/without pTBI. Fig 1 illustrates the study’s conceptual model.

**Fig 1 pone.0296325.g001:**
[figure not shown]
The study’s moderated-mediation model: The association between pTBI and neuropsychiatric symptoms (direct effect (c’)) as mediated by brain network connectivity (mediation (a*b)), and moderated by puberty stage.

### Aims and hypotheses

Based on the literature review, the present study proposes the following aims and hypotheses (as depicted in Fig 1):

**Aim 1**: Examine the moderating effect of puberty (pre- and post-pubescence) on the association between pTBI, brain network connectivity measures and neuropsychiatric outcome among females:

1.1. Examine the direct association between pTBI and neuropsychiatric outcome (Fig 1: direct effect c’ pathway). We hypothesize that females following pTBI will present poorer neuropsychiatric outcome as compared to healthy female controls.

1.2. Examine the relationship between pTBI and brain network connectivity measures (Fig 1: slope a pathway). We hypothesize that females with pTBI will present higher network connectivity measures and lower network efficiency compared to healthy female controls.

1.3. Examine the relationship between brain network connectivity measures and neuropsychiatric outcome (Fig 1: slope b pathway). We hypothesize that higher network connectivity measures and lower network efficiency will be associated with poorer neuropsychiatric outcome.

1.4. Examine the moderating effect of puberty on the mediated association between pTBI, brain network connectivity and neuropsychiatric outcome (Fig 1: mediation a*b pathway through moderator). We hypothesize that puberty will moderate the associations between brain network connectivity measures and network efficiency, and neuropsychiatric outcome in females post pTBI. That is, post-pubescence females compared to pre-pubescence females will show higher network connectivity measures, lower network efficiency and poorer neuropsychiatric outcome.

**Aim 2:** Examine the effect of changes in puberty stage and hormonal levels on brain network connectivity measures and neuropsychiatric outcome in pTBI females. We hypothesize that among females following pTBI, earlier changes in puberty stages (i.e. changes from one Tanner stage to another) and a significant increase in hormonal levels across recovery, will be related to higher network connectivity measures and lower network efficiency as well as to poorer neuropsychiatric outcome.

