#### Descriptive statistics

Descriptive statistics of variables will be obtained to understand the characteristics of the study population, to evaluate the distribution of participants across subgroups (e.g., puberty stage), and to identify potential confounders to inform subsequent analyses.

**Aim 1**- **moderated-mediation model:** To test our main study’s hypothesis we will apply a moderated- mediation model. Briefly, we will examine whether the magnitude of a mediation effect impact of mediator (*changes in brain network connectivity*) on the association between predictor (*pTBI*) and outcome (*neuropsychiatric outcomes*) is conditional on the value of a moderator (*puberty stage at T0*). The analysis of the moderated-mediation model will use Hayes’s (2013) PROCESS macro (Model 59) [73]. Bootstrapping method will test significance of the effects to obtain robust standard errors for parameter estimation [73]. This will produce 95% bias-corrected confidence intervals of these effects from 1000 resamples of the data. Confidence intervals that do not contain zero indicate significant effects at *p* < .05.

**Aim 2- effect of changes in puberty stage and hormonal levels on mediator and outcome:** Two step-wise linear regression models controlling for age and pre/post-injury factors in the 1st step; for the injury severity in the 2nd step; and for puberty stage and hormonal levels at T0 and T1, as well as the difference between both measures (i.e., *Δpuberty stages and Δhormonal levels*) in the 3^rd^ step, to predict (1) brain network connectivity and (2) neuropsychiatric outcomes, at T1 will be conducted.

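### Hypothesis 1.1 predicts an overall pTBI-versus-control difference but is tied to the direct effect c', which is a different and, on the protocol's own hypotheses, smaller quantity

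*Protocol article*

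**What the plan says.** In Aims and hypotheses, item 1.1 sets the task "Examine the direct association between pTBI and neuropsychiatric outcome (Fig 1: direct effect" c'). It then states the expectation: "We hypothesize that females following pTBI will present poorer neuropsychiatric outcome as compared to healthy female controls". The Fig 1 caption uses the same label: "The association between pTBI and neuropsychiatric symptoms (direct effect (c’)) as mediated by brain network connectivity (mediation (a*b)), and moderated by puberty stage". The article nowhere names a total effect and plans no group comparison that leaves the mediator out.

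Item 1.4 is introduced as "Examine the moderating effect of puberty on the mediated association between pTBI, brain network connectivity and neuropsychiatric outcome". Its first hypothesis sentence is also about moderation: "We hypothesize that puberty will moderate the associations between brain network connectivity measures and network efficiency, and neuropsychiatric outcome in females post pTBI". The sentence that then explains it says that "post-pubescence females compared to pre-pubescence females will show higher network connectivity measures, lower network efficiency and poorer neuropsychiatric outcome".

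The Aim 1 paragraph of the Analytical approach (under Descriptive statistics) plans PROCESS Model 59 and asks whether the mediation effect depends on puberty stage at T0. It gives one general rule, "Confidence intervals that do not contain zero indicate significant effects at" p < .05, and does not match effects to items 1.1 to 1.4. Exploratory analyses adds that the primary model examines each pathway on its own, and provides for partial mediation.

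**The concern.** A prediction that injured girls will do worse than healthy girls makes no reference to connectivity. It concerns the total effect. The label c' points to another parameter: the group difference among girls with the same connectivity change. If the label is followed, a real group difference that runs partly through connectivity is judged only on the part that does not. The more of the effect connectivity carries, the less of it is left to support 1.1. A study whose mediation theory is right could then report its first hypothesis as unsupported.

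The secondary issue is the explanatory sentence in 1.4. Post- and pre-pubescent girls may differ in mean connectivity and symptoms through normal maturation, in controls as well as in injured girls. The Introduction itself links puberty to mood symptoms and to structural connectivity in the absence of injury. Such a difference is neither necessary nor sufficient for moderation of the pTBI effect.

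**Working it through.** The plan states no figure for this point, so none can be reproduced. The point rests on setting the hypothesis beside its path label. The simulations only show how far apart the parameters can lie.

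**Sign of the gap.** In a linear mediation model, total effect = c' + a*b.
- Item 1.2 expects higher connectivity after pTBI (a > 0) and 1.3 links higher connectivity to poorer outcome (b > 0), so a*b > 0.
- For efficiency, 1.2 expects lower values (a < 0) and 1.3 links lower values to poorer outcome (b < 0), so again a*b > 0.
- Hence, if 1.2 and 1.3 are right, c' = total - a*b is less than the total effect.

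**Model 59.** The moderator acts on a, b and c'. There is one direct effect per puberty stage, and the pTBI coefficient in the outcome equation refers to the stage coded 0 unless puberty is centred.

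**Inputs.** From Sample size and power: 120 girls, 1:1, about 20% attrition, α = .05. So 120 × 0.8 = 96, or 48 per group. Assumed, because the documents give no values: the paths below, residual SD 1, binary balanced puberty, two-sided test, no moderation in these cases. There were 4,000 runs per case. The total-effect regression contained pTBI and puberty stage.

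| Case | a, b, c' | True difference c' + a*b | Total effect | c', simple mediation model | pTBI coefficient, Model 59 |
|---|---|---|---|---|---|
| Full mediation | 0.8, 0.6, 0 | 0.48 | 51.5% | 4.7% | 4.8% |
| Full, larger a | 1.0, 0.6, 0 | 0.60 | 69.2% | 5.5% | 5.4% |
| Partial mediation | 0.5, 0.39, 0.3 | 0.495 | 61.6% | 29.2% | 17.2% |
| Opposite signs | 0.8, 0.6, -0.48 | 0 | 4.7% | 57.2% | 32.4% |

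**Check by formula.**
- Full mediation, total effect: within-group SD of the outcome = √(1 + 0.6²) = 1.166; d = 0.48/1.166 = 0.41; noncentrality = 0.41 × √(48/2) = 2.02; power about 51%.
- Partial mediation, total effect: SD = √(1 + 0.39²) = 1.073; d = 0.495/1.073 = 0.46; noncentrality 2.26; power about 61%.
- Partial mediation, c': share of pTBI variance explained by the mediator = 0.0625/1.0625 = 0.059; SE = 1/√(96 × 0.25 × 0.941) = 0.210; 0.3/0.210 = 1.43; power about 29%.
- Same case, one puberty stage only (48 girls): SE = 0.298; 0.3/0.298 = 1.01; power about 17%.

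The opposite-signs case contradicts 1.2 and 1.3 taken together. It is included only to show that c' can also be significant when the groups do not differ.

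**Item 1.4, same N, assumed values.**
- Puberty main effects only (0.5 on the mediator, 0.7 on the outcome), no moderation: the post/pre contrast on outcome is significant in 81% of runs within pTBI and 98% overall; the connectivity-by-puberty interaction in 5%.
- Moderation of path b by 0.6, no puberty main effect: contrast 5%, interaction 80%.

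The interaction here stands for the moderation limb. The difference between conditional indirect effects was not itself simulated.

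**The case against.** Several counter-arguments have force.

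- **The label is not a decision rule.** The Aim 1 analysis paragraph does not say that c' will decide 1.1, the hypothesis sentence is sound as written, and the caption may be loose notation for the association being mediated. This softens the point but does not remove it. The label appears twice, each pathway is to be examined on its own, and no total-effect test is planned. A fuller plan might supply a mapping, but here the article states one, and it does not fit the hypothesis.
- **Full mediation is not the stated theory.** A reader might infer that c' is bound to be null if the study's theory holds. The documents do not support that: Fig 1 has both c' and a*b, and Exploratory analyses provides for partial mediation. Setting c' = 0 forces the 5% figure, so the partial-mediation case belongs beside it.
- **Nobody says only the reference-stage coefficient will be read.** True. The 17% applies only if that coefficient is taken as the answer.
- **Item 1.4 is mostly right.** A reader might infer that 1.4 will be judged on a puberty main effect, so that normal maturation could confirm the primary hypothesis. The documents do not support that either. The introduction to 1.4, its first sentence, the sample-size section and the Aim 1 analysis all specify moderation. Only the explanatory sentence departs from it.

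**Conclusion.** The mismatch in 1.1 stands: the hypothesis is a total-effect statement and its assigned parameter is c'. On the protocol's own signs c' understates the predicted difference, and under Model 59 there is one c' per stage. On assumed path values with 96 girls, the loss of detection runs from about 62% down to 29% (17% for the reference-stage coefficient) under partial mediation, to about 52% down to 5% under full mediation. The direction follows from 1.2 and 1.3; the size depends on values that the documents do not give. A non-significant c' would leave 1.1 unsupported; it would not show it to be false.

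For 1.4 the fault is limited to one sentence, which describes a mean difference by puberty stage and gives the moderation itself no direction. The planned model already contains the right test. Neither issue affects the sample size or the primary model. Severity is moderate.

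**What to change.** 1. Tie 1.1 to the total effect: regress the neuropsychiatric outcome on pTBI, with whatever covariates the primary model uses and without the mediator. Correct the label in 1.1 and in the Fig 1 caption.
2. Report c' for each puberty stage separately, as the direct component.
3. Replace the explanatory sentence in 1.4 with a directional statement that the indirect effect of pTBI through connectivity is larger in post- than in pre-pubescent girls. Judge it by the bootstrap confidence interval for the difference between the two conditional indirect effects. This matches the introduction to 1.4 and the Aim 1 analysis. If the authors mean moderation of the connectivity-outcome path alone, as the first sentence of 1.4 reads, they should say so and name that interaction instead.

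The cost is wording and one extra regression on data already to be collected. It should be settled before outcome data are analysed.
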